## Abstract

**Background:**

The nonmedical use of prescription opioids (NMUPO) in young adults in the United States is concerning and is robustly influenced by many psychosocial factors. Given the advantages of flexibility, wide coverage, and real-time responses and assessment, using social media appears to be a promising and innovative approach to delivering psychosocial intervention to young adults. However, few theory-based social media interventions are available for NMUPO targeting this at-risk population.

**Objective:**

Guided by the information-motivation-behavioral skills model, the proposed research aims to address critical gaps by theoretically exploring psychosocial content associated with NMUPO among young adults via formative assessment. These findings will then be used to develop and evaluate the feasibility and preliminary efficacy of a peer-led social media intervention to reduce NMUPO among young adults.

**Methods:**

The proposed study will comprise serial research activities. First, formative research will be conducted through semistructured interviews among 30 young adults engaged in NMUPO. Qualitative data will be synthesized using a pragmatic approach for identifying psychosocial content associated with NMUPO. Second, qualitative findings will be used for developing a peer-led social media intervention to reduce NMUPO among young adults by integrating promising psychotherapy principles and incorporating them with well-trained recovery coaches. Third, the social media intervention will be evaluated through a 12-week randomized controlled trial among 70 young adults (n=35, 50% in the intervention group and control group) engaged in NMUPO via mixed methods, including pre- and postintervention surveys, social media paradata (eg, time-series reactions to posts) collection, and ecological momentary assessment during the intervention. The control group will not receive an intervention but will complete the pre- and postintervention surveys. The primary outcomes will be feasibility, usability, and acceptability, while the secondary outcomes will be psychosocial and behavioral measures, such as past–3-month NMUPO, intention, psychological distress, self-efficacy, resilience, and coping strategies.

**Results:**

The proposed study was funded in May 2024. Social media campaigns have received responses from a total of 379 individuals, with 24 (6.3%) identified as eligible. As of February 10, 2025, we have completed formative interviews with 8 eligible participants.

**Conclusions:**

The proposed study will be one of the first efforts to develop and deliver a theory-based peer-led intervention on social media, incorporating empirical findings on the psychosocial mechanism of NMUPO. The findings of the proposed study will provide valuable insights into opioid risk reduction for young adults through an innovative approach. If the tested trial is found to be feasible, the proposed study will contribute to future scaled-up and fully powered psychosocial interventions among young adults and other key populations at risk for NMUPO.

**Trial Registration:**

ClincialTrials.gov NCT06469749; https://clinicaltrials.gov/study/NCT06469749

**International Registered Report Identifier (IRRID):**

DERR1-10.2196/65847

## Introduction

### Background

The nonmedical use of prescription opioids (NMUPO) is a critical public health concern in the United States, and young adults are particularly susceptible to this behavior. NMUPO refers to the aberrant use of prescription opioids in a manner other than as prescribed [1-3]. Substance use literature has paid increasing attention to NMUPO owing to its adverse consequences. National US data have shown a substantial increase of opioid-related overdose deaths, from <5000 in 1999 to >100,000 in 2023 [4,5]. NMUPO has also led to extensive medical costs in the United States (US $78.5 billion annually) [6]. Young adults (aged between 18 and 25 y) are at a high risk for NMUPO. In 2019, 5.5% of young adults in the United States engaged in past-year NMUPO, compared to 2.3% to 3.5% for other age groups. This rate was even higher among those who were not enrolled in college (6.3%) [7]. Besides the risk of overdose and dependence, NMUPO is associated with other negative outcomes, including health-jeopardizing behaviors (eg, driving under the influence), sexual risk behaviors, and suicide attempts [1,8-11]. In response to this issue, many US jurisdictions have launched initiatives to monitor prescription opioids [12]. Despite an obvious reduction in the prescribing rate (eg, 47% in 2019 to 38% in 2023) [12], NMUPO-related deaths remain high (>100,000 in 2023). Notably, NMUPO is strongly linked with the initiation of heroin and synthetic opioid use (eg, fentanyl) in young adults, posing a substantial risk for the development of substance use disorder (SUD) and overdose [13]. Hence, interventions targeting young adults are urgently needed to address NMUPO, and those should be delivered beyond the college population [14].

Interventions for NMUPO in young adults should take psychosocial factors into account. NMUPO literature has identified several important psychosocial factors associated with NMUPO in young adults, including perceived stress (eg, academic strain and traumatic stress), psychiatric distress (eg, depression and anxiety), perception of risk, peer and family influences, and sensation seeking [15-18]. [name] and his colleagues’ previous research on NMUPO in college students has indicated several additional factors that reduce risk for NMUPO, such as psychological resilience, positive coping, outcome expectancies, and self-esteem [10,19-21]. Importantly, psychosocial factors robustly contribute to NMUPO. A meta-analysis study revealed that pooled effect sizes of psychosocial factors on NMUPO (odds ratios 2.14-2.45) were higher than those of somatic symptoms (odds ratio 0.81-1.76), which are traditionally viewed as major NMUPO determinants [22]. These findings indicate that interventions should be guided by a structured framework between psychosocial factors and health actions for NMUPO.

There are a handful of interventions that have been recently developed to address psychosocial aspects of NMUPO in young populations [23-25]. Although these programs have shown some efficacy, they encounter numerous challenges. First, most programs have been adapted from existing substance use interventions that were not originally designed for NMUPO. For example, some content specific to opioids (eg, the risk for overdose and pain relief expectancy) are absent from these programs, yet these factors significantly contribute to health action related to NMUPO. Second, most programs were delivered in schools and failed to target young adults who did not attend college or were difficult to reach. Third, the flexibility of these interventions was limited because they were delivered by professionals in an in-person setting. Furthermore, literature on substance misuse prevention in young adults has revealed several drawbacks to the in-person context, such as limited trust and fear of being stigmatized [26]. These challenges highlight the critical need for an innovative intervention that is based on psychosocial theory, tailored to the NMUPO context, and flexible in real-world settings.

### Psychosocial Theoretical Framework for an NMUPO Intervention

To guide an intervention addressing psychosocial aspects of NMUPO, a theoretical framework (Figure 1) was developed based on the information-motivation-behavioral skills (IMB) model [27]. The IMB model has been applauded for its strength in considering a straightforward path diagram for health behavior changes [28]. This model emphasizes that health behavior changes are driven by 3 arrays of psychosocial constructs—information, motivation, and behavioral skills. Information refers to knowledge contributing to a prerequisite for enacting the changes (eg, misinformation of opioids). Motivation includes 2 belief components: personal motivation (eg, outcome expectancies and risk perceptions) and social motivation (eg, social norms and support). Behavioral skills stand for cognitive capacities (eg, self-efficacy and resilience) and behavioral skill sets necessary for adopting the changes (eg, coping or self-regulation skills) or for managing barriers (eg, stress management) [27,28]. Information and motivation can directly affect the target behavior as well as indirectly affect it through the acquisition of adjacent behavioral skills. Such a well-structured framework offers clear guidance for intervention practices and suggests that intervention delivery could benefit from targeting information and motivation factors in the initial sessions, along with enhancing the role of behavioral skill training gradually in the intervention. For instance, initial efforts ought to address misinformation and outcome expectancies of substance use, and, as the intervention progresses, sessions should facilitate action by helping participants develop planning strategies and coping skills. Indeed, existing evidence has shown the efficacy of IMB-guided interventions in reducing substance use (ie, tobacco and illicit drugs) [29-32]. Thus, the IMB model is an ideal theoretical choice for developing an intervention for NMUPO.

**Figure 1 figure1:**
[figure not shown]
Theoretical framework for the proposed study. NMUPO: nonmedical use of prescription opioids.

### Social Media as a Promising Platform for an NMUPO Intervention Targeting Young Adults

The rapid development of social media technologies provides a novel tool for substance use interventions. Increasing substance use literature has highlighted the significant potential of social media, in which individuals can obtain substance use knowledge, communicate their experiences and thoughts of substance use problems, and seek out social support from peers with similar problems through available networks or groups [33,34]. It is worth noting that social media offers distinct merits in addressing existing challenges in interventions for NMUPO in young adults. First, recent research has validated the use of social media to reach people who engage in NMUPO from multiple venues across the United States [35,36]. Ubiquitous connectivity enables interventions to deliver content remotely to young adults who are not enrolled in college and, therefore, not able to access traditional models of education on safe substance use. Second, social media allows interactive posts in multiple formats (eg, texts, images, polls, and videos) and with customized functions (eg, internet-based goal setting tools and notifications) without time restrictions. This can facilitate exposure to intervention content at the time when participants choose to engage [37]. Third, social media technologies are applicable to timely measurements, such as ecological momentary assessment (EMA) and paradata (eg, auxiliary data of engagement [frequencies of shares, comments, and “likes,” etc] analyses) [38,39], which allow tracking of intervention usability and acceptability on specific modules in real time. Extant literature has shown that EMA has been applied in intervention research for substance use reduction and psychosocial improvements [40]. Fifth, social media is extremely popular among young adults. The latest national data indicate that 72% of US adults use social media, most of whom are young adults (84%) who use it daily (70%) [41].

Another notable feature of social media is that it is significantly favorable for the peer role model, which has been a robust intervention approach for reducing substance use, particularly among young adults [42]. Existing evidence has demonstrated that social media interventions are effective in promoting behavior change for stigmatizing behaviors, including substance use, with perceived peer influence and support playing an important role in the change [43]. Accordingly, emerging peer-led intervention programs have been initiated on popular social media platforms among young adults (ie, Instagram [Meta Platforms, Inc], Facebook [Meta Platforms, Inc], Snapchat [Snap Inc], and Twitter [subsequently rebranded X; X Corp]) and have indicated good feasibility and preliminary efficacy in reducing various substance use behaviors (eg, risky drinking, cigarette use, and cannabis use) [37,42-47]. Notably, promising findings have also been reported for NMUPO reduction. Young et al [45] conducted a pilot study of a peer-led trial on Facebook for patients with chronic pain, who were randomly assigned to the peer-led intervention group or the control group (with no peer leaders) The preliminary results suggested higher engagement and more discussion on NMUPO and coping in the intervention group than in the control group. Taken together, the advantage for the peer role model with other promising aspects, social media appears to be a promising platform for NMUPO intervention among young adults, and such programs would be strongly powered by psychosocial theory–guided content and peer-led modules.

### The Aims of This Study

#### Overview

This study proposes to develop and pilot-test a theory-guided, peer-led social media intervention on Instagram as well as examine its feasibility and preliminary efficacy among young adults engaged in recent NMUPO via a randomized controlled trial (RCT). The assessments will use mixed methods to collect various types of data, including qualitative assessment of semistructured interviews; psychometric measures in pre- and postintervention surveys; real-time paradata on social media platforms; and brief, timely measures in EMA surveys during the intervention. The specific aims are mentioned below.

#### Aim 1

Aim 1 involves conducting a formative study to inform a theory-based social media intervention for NMUPO among young adults in the United States. By collaborating with 4 peer leaders trained as “recovery coaches,” the proposed study will recruit 30 young US adults (aged 18-25 y) who engage in NMUPO from social media (eg, Instagram) and conduct in-depth semistructured interviews to explore psychosocial content associated with NMUPO. The interviews will be guided by the IMB model.

#### Aim 2

Aim 2 involves developing a theory-based social intervention to reduce NMUPO among young adults. The intervention will be developed upon findings from the formative study and based on several promising strategies (eg, peer support group, ambivalence resolving techniques, interactive training modules, internet-based goal setting, and video modeling). It will be delivered via Instagram private groups by peer leaders, with close supervision provided by experts and clinicians in the fields of health psychology and addiction medicine.

#### Aim 3

Aim 3 involves testing the feasibility and preliminary efficacy of the theory-based social media intervention with a randomized controlled design for NMUPO among young adults. Participants who engage in recent NMUPO will be randomly assigned to 1 of the 2 parallel groups, including the intervention group (35/70, 50%) and control group (35/70, 50%), using a 1:1 allocation ratio. The intervention will be evaluated in terms of feasibility, usability, acceptability, engagement, dose, and preliminary efficacy using mixed methods (eg, surveys, EMA, paradata, and semistructured interviews). During the intervention, EMA (a prompt every 2 days) will assess the acceptability and usability of individual modules. Preliminary efficacy will be tested on behavioral outcomes (ie, past-month NMUPO) and psychosocial factors (eg, outcome expectancy, self-efficacy, action or coping planning, resilience, and psychiatric symptoms).

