#### Participants and Recruitment

Participants for the formative study and intervention trial will be those who meet the following inclusion criteria: (1) aged between 18 and 25 years, (2) US residents, (3) engaged in NMUPO in the past 3 months, and (4) using Instagram at least 3 times a week in the past 3 months. NMUPO refers to the occurrence of the following behaviors (1 time or more): (1) taking a prescription opioid without a prescription, (2) taking more doses than prescribed, and (3) using opioid for a nonmedical reason (eg, getting high) [1-3]. Individuals will be excluded if they report (1) receiving substance use interventions in the past 3 months, (2) being diagnosed with SUD, or (3) not being proficient in English. We anticipate a total sample size of 100, with 30 for the formative study and 70 for the intervention trial.

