##### Intervention Components

###### Overview

The proposed intervention components are guided by the IMB-based conceptual framework (Figure 1), with each component targeting specific factors derived from 3 psychosocial constructs (ie, information, motivation, and behavioral skills). As outlined in the framework, the pacing of intervention is structured to prioritize addressing information and motivation factors during the initial phases, while later sessions progressively promote behavioral skill training that contributes to psychological distress management and NMUPO reduction. Incorporating Instagram functions, the intervention platform is proposed to consist of four intervention modules, including (1) NMUPO knowledge module, (2) self-care module, (3) internet-based goal setting or monitoring module, and (4) peer support module (Figure 3). These are planned, and final content will be informed by or modified in line with the formative research. The research team will work closely with the community advisory board and peer leaders to ensure appropriate content and language. The intervention will last 12 weeks according to previous social media trials (typically 8-12 wk) [37,44,79-86]. Clinicians will review the intervention materials and ensure the scope is appropriate. Content will be prompted daily as suggested by the IMB model (eg, initially focus on information and motivation factors and gradually enhance the role of behavioral skills).

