##### Web-Based Pre- and Postintervention Surveys

The web-based pre- and postintervention surveys will be developed and administered on REDCap [94] to measure demographic variables as well as psychosocial and behavioral factors outlined in the IMB-based conceptual framework. Factors include NMUPO behaviors (past–3-month NMUPO) and information- and motivation-related factors (ie, NMUPO knowledge, NMUPO risk perception, outcome expectancies, self-efficacy, psychological distress, resilience, and other substance use). Web-based surveys will be conducted among participants in both the intervention and control groups. Participants will receive survey links via inbox messages to the Instagram accounts they provide for the study. The preintervention survey will be sent 2 weeks before the intervention (baseline), and the postintervention survey will be sent in the week immediately following the intervention (12-week follow-up). The survey will be self-administered and take approximately 20 to 30 minutes to complete. If participants cannot complete the surveys at one time, they can save their responses, and the platform will generate a code that allows them to resume the survey within the same week. The survey will also provide forward and back buttons, allowing participants to review and change their responses before they submit their surveys. Study IDs and filling time will be collected for determining duplicate entries. e-gift cards will be provided for the completion of surveys (baseline and 12 weeks; US $30 each).

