##### NMUPO Measurement

The past–3-month NMUPO will be measured using relevant items from the Tobacco, Alcohol, Prescription medication, and other Substance use tool [100]. The scale includes 2 sections, with a screener followed by a brief assessment. The screener contains 1 item asking the frequency of NMUPO (ie, used just for feeling, more than prescribed, or without a prescription) with 5 response options (daily or almost daily, weekly, monthly, less than monthly, or never). Participants with a response other than “never” will be led to the brief assessment, including 3 dichotomous questions regarding their level of use, dependence, and concern from others related to the past–3-month NMUPO. The sum score of the brief assessment will be calculated, with a higher score indicating a greater level of NMUPO.

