## Discussion

### Anticipated Findings

In response to the growing evidence on psychosocial aspects of opioid addiction and relevant disorder concerns in the United States, this proposed study aims to apply a psychosocial theoretical framework and peer role model techniques to develop and implement an evidence-based intervention for reducing NMUPO risk in young US adults. The intervention will be established through a serial research activity, from a formative semistructured in-depth interview study to feasibility evaluation of a 12-week interactive peer-led trial. By leveraging the merits of social media, the proposed intervention study will be powered by adopting innovative approaches, including a tailored recruitment strategy (eg, paid advertisement campaigns), intervention delivery that transcends time and space constraints, and the application of mixed methods and time-series assessments (eg, paradata and EMA measures). As one of the first attempts to deliver peer-led interventions on social media specifically targeting NMUPO, the findings from this mixed methods design will offer valuable insights into the use of innovative approaches for reducing opioid risk among young adults. In line with previous intervention studies for NMUPO on social media [45], we anticipate that our intervention will yield high feasibility outcomes. In particular, the mixed methods assessments for the intervention group will demonstrate (1) high feasibility, acceptability, and usability on all intervention modules among young adults across 12 weeks and (2) high engagement, especially for the modules in the interactive formats, such as discussion polls and live streaming group meetings. We also anticipate significant preliminary intervention efficacy on the NMUPO-related and psychosocial behavior outcomes. Compared to the control group, the intervention will report (1) decreases in past–3-month NMUPO and other substance use (eg, alcohol, illicit drugs, and cigarettes), (2) decreases in psychological distress, (3) changes in outcome expectancies (eg, increased physical discomfort and decreased pain reduction), (4) increases in NMUPO knowledge and NMUPO risk perception, and (5) increases in resilience and self-efficacy (ie, action and coping).

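### Aim 3 names past-month NMUPO as the behavioural outcome but only a past-3-month measure is described, and that look-back spans the whole 12-week programme, which dilutes within-programme change

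*Protocol article*

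**What the plan says.** The Aim 3 paragraph of the Introduction gives the behavioural efficacy outcome as a definition, not an example: "Preliminary efficacy will be tested on behavioral outcomes (ie, past-month NMUPO".

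Four other places give a different window for the same outcome:

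- Abstract, Methods: "psychosocial and behavioral measures, such as past–3-month NMUPO".
- Web-Based Pre- and Postintervention Surveys: "Factors include NMUPO behaviors (past–3-month NMUPO".
- NMUPO Measurement: "The past–3-month NMUPO will be measured using relevant items from the Tobacco, Alcohol, Prescription medication, and other Substance use tool".
- Anticipated Findings: "decreases in past–3-month NMUPO and other substance use".

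Eligibility uses the longer window as well: "engaged in NMUPO in the past 3 months".

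On timing, the baseline survey is sent two weeks before the programme starts, the programme lasts 12 weeks, and "the postintervention survey will be sent in the week immediately following the intervention (12-week follow-up". This is the only outcome assessment after baseline. On content, the Intervention Components overview puts information and motivation first, "while later sessions progressively promote behavioral skill training that contributes to psychological distress management and NMUPO reduction".

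The NMUPO measure has two parts. A screener gives a five-level frequency answer, running from daily use down to never. Anyone above never then gets three yes/no items on the past 3 months, covering how much is used, dependence, and whether others are worried. Their sum is the score.

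**The concern.** There are two separate problems.

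First, the outcome is defined in two incompatible ways. The only instrument named for NMUPO as an outcome is tied to 3 months. As written, the trial will not collect the quantity that Aim 3 says will be tested, and a 3-month result would not answer the aim as stated.

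Second, the 3-month window is almost exactly as long as the programme. The follow-up value therefore pools use before the programme could have worked with use after it. The programme builds its behavioural skills up towards the later weeks, so the window gives full weight to the weeks before most of that training.

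Nothing else in the data recovers the timing. The ecological momentary assessments measure acceptability, usability and dose, not opioid use, and only in the intervention arm. Controls complete only the two surveys. The pilot is meant to inform a larger trial, so a diluted behavioural signal could mislead its planning.

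**Working it through.** The plan gives no figure on this point to reproduce. The check is calendar arithmetic.

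**Inputs from the protocol article.** Programme on days 1 to 84 (12 × 7). Post survey in the following week, days 85 to 91. Baseline survey at day −14.

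**Assumptions.** Three months is 90 to 92 days and one month is 30 days. The window ends the day before the survey, so it runs from (survey day − look-back) to (survey day − 1).

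**Coverage of the 3-month window**

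- 90 days, survey on day 85: days −5 to 84. All 84 programme days and 6 earlier days.
- 90 days, survey on day 91: days 1 to 90. All 84 programme days and no earlier days.
- 92 days, survey on day 85: days −7 to 84. All 84 programme days and 8 earlier days.

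Across 90 to 92 days and days 85 to 91, all 84 programme days are always covered, with 0 to 8 earlier days. To answer *never*, the last use must fall on day 0 at the latest. If completion slips a further week, to day 98, a 90-day window runs from day 8 to day 97 and still covers 77 of 84 days.

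**Coverage of the window named in Aim 3 (30 days)**

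- Survey on day 85: days 55 to 84, which is 30 programme days.
- Survey on day 91: days 61 to 90, which is 24 programme days.

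A participant whose last use was by day 54 to 60, depending on survey day, could answer *never*.

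**How far the frequency answer can move.** Take an assumed weekly user surveyed on day 88 who stops at the end of week *k*. The 90-day window is days −2 to 87, so days with ongoing use number 7*k* + 3, and expected uses are (7*k* + 3)/7. The 30-day window is days 58 to 87, so days with ongoing use are 7*k* − 57, or zero if negative.

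| Stops at end of | Uses in 90 days | Same, per 30 days | Uses in last 30 days |
|---|---|---|---|
| Week 4 | 31/7 = 4.4 | 1.5 | 0 |
| Week 8 | 59/7 = 8.4 | 2.8 | 0 |
| Week 10 | 73/7 = 10.4 | 3.5 | 13/7 = 1.9 |
| Week 12 | 87/7 = 12.4 | 4.1 | 27/7 = 3.9 |
| Does not stop | 90/7 = 12.9 | 4.3 | 30/7 = 4.3 |

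On the 3-month item, an early stop can move the answer from weekly towards monthly, and a stop at week 10 or later hardly changes it. On a 30-day item, a stop by week 8 reads as zero.

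**Overlap of the two 3-month windows.** The surveys are 85 + 14 = 99 to 91 + 14 = 105 days apart, which exceeds 92, so the baseline and follow-up windows do not overlap.

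**The case against.** The strongest defence is that the 3-month window is a legitimate choice and the Aim 3 phrase is a slip. The Abstract, Methods and Discussion agree with each other and with the eligibility criterion. Use over the whole programme is a reasonable target. Both arms answer the same items at both surveys and the two windows do not overlap, so pre-post change and the between-arm contrast can be measured. On this view, correcting one phrase is enough. Replacing the 3-month measure would also carry a cost: one episode in 3 months is enough for entry, so some participants may report nothing in the baseline month, in a sample of only 70.

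Most of this stands, and it argues for keeping the 3-month items. It does not remove the contradiction. Correcting the phrase alone would leave end-of-programme use unmeasured.

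A reader might infer that stopping during the programme is invisible, or that the outcome is a plain yes/no on any use. The documents do not support either. The screener is graded and can fall with an early stop. A single early use opens the three scored items but does not by itself mean that all are endorsed.

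A reader might also scale the planning effect by the share of the window after some onset week. The documents do not support that. They give no onset, and the theory section says that information and motivation, which come first, can change behaviour directly as well as through skills. The effect sizes in the Power Analysis (−0.17 to −0.34) come from a 6-month follow-up. Neither an ordinal answer nor a sum of three items need scale in proportion to time.

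**Conclusion.** The concern holds in this form. The recall window for the behavioural outcome is contradictory: one passage says past month, four say past 3 months, and no past-month measure is described. Under the 3-month window, the follow-up covers all 84 programme days whenever the survey is answered in its planned week, so stopping during the programme cannot register as *never*.

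Within-programme change is diluted by an amount that depends on when it occurs. In the worked example it is substantial but visible for a stop at week 4 (4.4 against 12.9 uses) and nearly invisible from week 10 (10.4 against 12.9). These counts assume a weekly user, an abrupt and complete stop, accurate recall and a survey on day 88. No attenuated effect size can be derived from the documents.

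This should be fixed, but it is not critical: the outcome is secondary, and the primary outcomes are feasibility, usability and acceptability.

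**What to change.** Reconcile Aim 3 with the Abstract, the survey section, NMUPO Measurement and Anticipated Findings, so that one pre-specified recall window defines this secondary outcome throughout.

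Add one past-30-day NMUPO frequency item, worded identically in the pre and post surveys of both arms. The outcome named in Aim 3 is then measured and use at the end of the programme can be seen. Keep the existing 3-month items alongside it for eligibility, description and use over the whole programme. State which of the two carries the efficacy comparison and report the other as supporting.

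The cost is one extra item at two time points and some wording changes. The drawback is that infrequent users may report zero in the baseline month and so cannot show a reduction on that item, which is a reason not to drop the 3-month items. The Results section plans the Aim 3 ethics submission for early 2027 and recruitment for late 2027, so the change can still be made. After the baseline surveys are collected, the missing past-month value cannot be recovered.
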